### Qualitative data analysis

Interviews will be analysed using thematic analysis.^57^ A descriptive coding scheme will be developed from transcripts and based on participants’ perceptions and experiences. Two types of coding will be used: ‘open coding’ to locate themes followed by ‘focused coding’ to determine which themes repeat often and which represent unusual concerns. Two researchers (KI and [name]) will read and code the interviews separately to develop and agree on a list of themes that reflect the participants’ own views and experiences. Coding will proceed in an iterative way with detailed memos linking emergent themes. The perceptions and views of different participants will be compared using constant comparison. A software program (NVivo V.12)^58^ will be used to facilitate data analysis. To ensure data validation the following strategies will be used: data triangulation (collecting data from different groups of participants), multiple coding and respondent validation, which involves cross-checking interim research findings with respondents.

### Progression criteria

Criteria that will be used as guidance to assess the feasibility of progressing to a future randomised controlled trial^59–61^ will include:

Prevalence: A high prevalence (≥80%) of either frailty or sarcopenia may indicate no need to assess, and therefore care pathways should assume patients have frailty and/or sarcopenia. A low prevalence (<10%) would indicate that assessment may not be appropriate in this population.Acceptability of assessing frailty and sarcopenia in the fracture clinic: <50% of patients with complete assessments of frailty or sarcopenia to indicate assessment is not feasible. The Trial Steering Committee will consider if protocol changes are practical to improve completion rates and therefore feasibility.Recruitment: At least 80% of patients to be recruited within 1 year of start of recruitment.

Not fulfilling the above criteria does not necessarily indicate failure but rather indicates changes to be made to protocol before proceeding to a definitive trial (figure 1).

**Figure 1 F1:**
[figure not shown]
Study recruitment and follow-up diagram.

Progression criteria will be reviewed by an independent Trial Steering Committee to determine if it is feasible to proceed to a definitive trial and if any protocol changes are required. Recruitment rates will be calculated by the number/proportion of eligible patients approached who agreed to participate. Adherence to protocols and completion rates will be examined by reporting the number/proportion of patients who complete the baseline and 6 months’ follow-up assessments.

### Health economic data analysis

Appropriate published national data: British National Formulary, National Reference Costs, Unit Costs of Health and Social Care (Personal Social Services Research Unit)^55^ and/or local (from hospital finance and trial manager) unit costs will be applied to itemised resource usage in calculating the total costs of the intervention and other NHS service usage. We will apply the UK tariff to translate the EQ-5D-5L and ICECAP-O questionnaire to utility scores.

Economic analyses in both costs and quality of life will be descriptive, reported as means with their SD. Correlation before utility scores with the main outcome (ie, number of falls prevented) will be analysed to see if there is evidence of sensitivity.

We will test the sensitivity and feasibility of both instruments with this patient group to inform which to use in a future trial.

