Despite the increasing evidence for the association of fractures with frailty and sarcopenia, the two conditions remain under-recognised and therefore undertreated in patients with fragility fractures.^26 33^ Exercise and adequate nutrition, particularly with regard to vitamin D, calcium and protein, are key lifestyle approaches that can optimise bone, muscle and functional outcomes in older people, if they are individually tailored and appropriately prescribed.^27 34^

Early identification and treatment of sarcopenia has been suggested to be an important element in the future prevention of fractures.^35 36^ Comprehensive geriatric assessment (CGA)—a method of identifying and treating an older person’s medical, functional and psychosocial problems by multidisciplinary health and social care teams—can offer an opportunity to manage these age-related syndromes and improve health outcomes.^37^ A recent study has reported that CGA can help identify those with an increased risk of hip fractures allowing the implementation of prevention strategies.^38^ The aim of this study is to evaluate the feasibility of assessing people aged 65+ years, who attend fracture clinic with an upper limb fracture, for frailty and sarcopenia in addition to routine assessment for fracture risk due to osteoporosis. We will demonstrate whether it is practical and acceptable (to patients and staff) to assess for frailty and sarcopenia in a busy fracture clinic typical of those found in every general hospital, and then further manage these patients through geriatric clinical services. This feasibility study will inform a future randomised controlled trial.

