### Setting and participants

This is a mixed-methods feasibility study. Patients will be recruited from three fracture clinics in one acute hospital over 12 months (March 2019 to March 2020). Patients will be eligible to take part in the study if they are aged 65+ years, have a single arm fracture (wrist or upper arm), referred directly from Accident & Emergency, general practice, local minor injuries unit or other fracture clinics, able to give informed consent and not previously diagnosed with frailty and/or sarcopenia. Patients with pathological fractures, multiple or lower limb fractures, active cancer diagnosis or care home residents will be excluded.

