### Intervention

Patients attending fracture clinics will be assessed for frailty and sarcopenia, in addition to their usual care. Patients identified as having either frailty or sarcopenia will be referred to existing local geriatric clinical services for specialist review including CGA. This is a multidisciplinary assessment and management of patients using health and social care pathways. These may include medical review of comorbidities and optimisation of medication; consideration of unmet needs in physical, cognitive and social domains; and referrals to other clinical, social care or voluntary services. These actions and referrals will be varied and focused on the individual patient’s recognised needs and their wishes.

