### Feasibility outcomes

*Feasibility of assessing frailty and sarcopenia among patients with upper limb fracture*: This will be determined by: (A) the percentage of people who are assessed by each tool (adequacy); (B) availability of required data and the number of missing data; (C) equipment (including cost, availability of functioning equipment and frequency of calibration); (D) the time for carrying out each assessment; and (E) acceptability of the tools by staff and patients (via interviews). This will determine the prevalence of frailty and sarcopenia among the study participants and which measures of assessing frailty and sarcopenia are most feasible in this population*Feasibility of using existing care pathways*: Patients identified as having either frailty or sarcopenia will be referred to local geriatric clinical services for specialist review as outlined in the intervention. The actions instigated from these assessments and referrals will be varied and individualised according to patient’s needs and wishes. These referrals may lead to additional attendance at outpatients, primary care or exercise classes, for example. We will report the number of patients identified to have frailty and/or sarcopenia who are referred to CGA, the number of those who receive CGA and the number and type of follow-up interventions.*Falls and fractures*: Participants will be asked to fill in a falls diary recording the date, suspected cause, location and the consequences of each fall. They will be contacted by telephone at 3 and 6 months after recruitment to collect self-assessed information on falls and fractures within the previous 3 months. This will establish whether quarterly data collection is suitable for the future trial.*Mortality*: Death rates within 6 months of recruitment will be collected from the hospital patient administration system (PAS).*Future outcome measures*: Baseline data on nutritional, physical and cognitive factors which may be associated with frailty and sarcopenia status will be collected. Quality of life and physical function will be measured at baseline, and 3 and 6 months after recruitment. The feasibility of using each of these assessments in this patient group will inform which instrument will be used in the future trial.*Healthcare resource use*: Testing the key resource usage of the intervention and downstream influence on service usage including those associated with referrals coming from the CGA process.*Quality of life*: Quality of life will be measured by EuroQual-5 dimensions-5 levels (EQ-5D-5L) and ICEpop CAPability measure for Older people (ICECAP-O). We will explore which instruments will be more sensitive in measuring quality of life changes for our study population and how often we should collect such information.

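### The sensitivity check for EQ-5D-5L and ICECAP-O uses falls prevented, a variable that no participant in this uncontrolled study can have; it should use observed falls

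*Protocol article*

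**What the plan says.** All references are to the protocol article.

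- **Health economic data analysis** gives one specific analysis of sensitivity: "Correlation before utility scores with the main outcome (ie, number of falls prevented) will be analysed to see if there is evidence of sensitivity". The purpose follows: "We will test the sensitivity and feasibility of both instruments with this patient group to inform which to use in a future trial".
- **Feasibility outcomes** (quality of life item) states the question to be answered: "We will explore which instruments will be more sensitive in measuring quality of life changes for our study population".
- **Setting and participants** gives the design: "This is a mixed-methods feasibility study". **Intervention** adds: "Patients attending fracture clinics will be assessed for frailty and sarcopenia, in addition to their usual care", and then: "Patients identified as having either frailty or sarcopenia will be referred to existing local geriatric clinical services for specialist review including CGA". No allocation and no control group are described. The randomised comparison comes later: "This feasibility study will inform a future randomised controlled trial" (Introduction).
- **Falls data** are a history taken at baseline, a diary, and telephone calls: "They will be contacted by telephone at 3 and 6 months after recruitment to collect self-assessed information on falls and fractures within the previous 3" (Feasibility outcomes; the unit is months). Quantitative data analysis summarises falls as counts, percentages, means and medians.

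**The concern.** A prevented fall is the difference between the falls that occurred and those that would have occurred without the intervention. This study has nothing from which to estimate the second quantity. Even a randomised trial would supply it only as a contrast between groups, never as a value for each patient that could be paired with that patient's utility score. The variable named in the sentence is therefore not available.

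The label is also out of step with the rest of the article. Falls are one of several items under Feasibility outcomes, and no other section designates a main outcome.

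At stake is part of the fourth study objective, the choice of outcomes for the future trial. The evidence on which instrument responds better to change would be missing or improvised. The natural improvisation is to count a fall in falls since baseline as prevention, and that would mislead.

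**Working it through.** **1. The plan's own figures.** The sample size statement reproduces: 80 / (1 − 0.20) = 100. The stated precision around 7% matches the upper side of an exact 95% interval (6.9 points at n = 100, 8.0 points at n = 80). No number in the article is in dispute here; the fault is in the variable.

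**2. What the variable needs, against what the study has.**

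| Needed for falls prevented | Available |
|---|---|
| Falls observed under the intervention | Yes: diary, and calls at 3 and 6 months |
| Falls expected without it | No: everyone is assessed, and everyone with either condition is referred |
| A value for each participant | No: it exists only as a group contrast |
| A definition or derivation | None in Feasibility outcomes, Table 1 or Quantitative data analysis |

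Participants with neither condition cannot stand in as controls. They differ from those referred by definition, and the Introduction itself treats frailty and sarcopenia as risk factors for falls.

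**3. Why a before-after difference does not rescue it.** First, the windows differ. The baseline history (Baseline data) covers previous years with no stated length, while each follow-up call covers 3 months. Secondly, patients are seen typically a few weeks after a fracture (Recruitment), often one caused by a fall (Introduction), so the baseline count is raised by selection.

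The size of the selection effect can be illustrated under assumptions that are not in the documents: equal 6-month windows, everyone enrolled after at least one fall, individual fall rates that do not change, and no intervention effect. Let X be the falls in one window, gamma-Poisson with mean m and dispersion k. Then

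expected drop = P(X = 1) / P(X ≥ 1), with P(X = 0) = (1 + m/k)^−k and P(X = 1) = m(1 + m/k)^−(k+1).

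- 0.35 falls a year, k = 2: m = 0.175, P(0) = 0.8456, P(1) = 0.1361; drop = 0.1361 / 0.1544 = 0.88 per person.
- 0.8 falls a year, k = 0.5: m = 0.40, P(0) = 0.7454, P(1) = 0.1656; drop = 0.1656 / 0.2546 = 0.65 per person.

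Over rates of 0.35 to 0.8 a year and k from 0.5 to 2, the drop is about 0.65 to 0.88 falls per person with nothing prevented. A simulation gave the same range.

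**4. Can observed falls be used instead?** Table 1 schedules falls, EQ-5D-5L and ICECAP-O at baseline, 3 and 6 months, and the calls cover exactly the intervals between those visits. The data are there.

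Precision is modest. For an assumed r = 0.30 with 80 patients: atanh(0.30) = 0.3095; 1.96 / √77 = 0.2234; limits 0.0862 and 0.5329; back-transformed, 0.09 to 0.49. This formula presumes roughly bivariate normal data, which fall counts are not. If the Abstract's general figure of 35% falling per year applied at a constant rate, 0.65^0.25 = 90% would have no fall in 3 months and 0.65^0.5 = 81% none in 6 months. That is about 8 and 16 fallers among 80. This cohort may well fall more often, so these counts are only indicative.

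**5. Barthel.** Table 1 and the section on data collected at follow-up place Barthel at baseline and 6 months only. The item on future outcome measures says that physical function is measured at 3 months as well. Only the baseline-to-6-month change is certain to be available.

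**The case against.** The strongest reply is that only a label is wrong. The sentence is visibly garbled (the word before is probably a slip for between or of), the rest of the article treats falls as observed counts, and a correlation of utility with number of falls can be run on the planned data. This stands in part. The remedy is indeed to restate the variable. But the sentence as printed names a specific and different quantity, so this is not detail left to a fuller document.

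A reader might infer that the choice between instruments is left without any evidence. The documents do not support that. Quantitative data analysis plans descriptive summaries of change in quality of life from baseline to 6 months, Health economic data analysis reports means with SD, and feasibility of each instrument is also to inform the choice. What is lost is the only specific analysis of sensitivity.

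A reader might also infer that the plan intends to correlate score levels rather than changes, or to count a before-after drop as prevention. The article says neither. It does not state which scores or time points enter the correlation, and no section plans a before-after count. These are ambiguities that the rewording should close.

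**Conclusion.** The point holds for the named variable. Falls prevented has no value for any of the 100 planned participants, so the correlation cannot be computed as written, and the term main outcome has no support elsewhere in the article. The conclusion rests on reading the study as having a single group. The article does not use that term, but it follows from the Intervention section and from the randomised trial being placed in the future. It does not depend on the illustrative fall rates.

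Severity is moderate to minor. It would be too much to say that the economic analysis or the feasibility study fails: this is a secondary, descriptive analysis, and the sample size, prevalence and agreement analyses and progression criteria are untouched.

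**What to change.** Delete the references to a main outcome and to falls prevented, and replace the sentence with wording such as:

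> For each of EQ-5D-5L and ICECAP-O, the change in score from baseline to 3 months, 3 to 6 months and baseline to 6 months will be correlated with the number of falls recorded in the same interval. The change from baseline to 6 months will also be correlated with the change in Barthel score over that period. Results will be given with 95% confidence intervals.

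Standardised response means for the two instruments in the same patients may be added descriptively; this is optional.

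Reconcile the Barthel schedule between the item on future outcome measures and Table 1. If 3-month Barthel scores are in fact collected, the shorter intervals can be added.

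The cost is analysis wording only, with no new data. The downside is that the correlations may be imprecise because many participants may have no falls, and the text should say so.

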### Ethics and dissemination

The study also obtained an ethical opinion for conduct by University of Southampton, Faculty of Medicine Ethics Committee and Research Governance Office. A consent form will be obtained by the research team from each participant prior to recruitment and another consent form will be obtained from those invited for interviews. Confidentiality and privacy will be ensured for all participants and the information gathered will only be used for scientific purposes. All participant information will be identified only by a study ID number. All data will be stored on a password-protected computer or in a locked filing cabinet in a secure office in our research unit and will be accessible only by the research team. In the analysis of results, data will be used anonymously and non-attributable to any individual. Our procedures for handling, processing, storing and destroying data are compliant with the Data Protection Act 2018. We will comply with Good Clinical Practice guidelines and the R&D measures of recording any serious adverse events (SAE) and reporting them immediately to the sponsor. Any incidents that result in hospitalisation, life threatening or death will be reported as SAEs immediately to the sponsor. The immediate reports will be followed promptly by detailed written reports. The immediate and follow-up reports will identify participants by their unique ID code that was assigned to the participant rather than their identifiable information such as name and/or address.

The study team will meet together monthly during the trial and will be responsible for ensuring high-quality delivery of the trial according to the agreed key milestones and deliverables. This will include early identification of potential problems, and implementing solutions to overcome them. A Trial Steering Group has been established to include the research team and external experts in the field who will meet every 6 months to oversee the study delivery and review the progression criteria. Amendments of any significant changes to the study design will be submitted to the relevant ethical committee to seek approval before implementation.

Findings from the study will be published in peer-reviewed high-impact journals and/or specialist open access journals. Research findings will be presented locally, nationally and internationally. We will work with our PPI team to further develop and implement the dissemination and engagement strategy including the development of reports and approaches to engage the community. We will disseminate the findings via social media (Facebook and Twitter), local groups and third sector, for example, Age UK and National Osteoporosis Society.
